### Objectives

The primary objective of this study is to assess the impact of telemonitoring on quality of life (QoL) in patients with inflammatory bowel disease (IBD). Secondary objectives include evaluating disease activity, the incidence of IBD relapses, and the rate of leukopenia in patients receiving immunomodulatory treatments (e.g., thiopurines, cyclosporine, tacrolimus). Additionally, the study will investigate medication adherence, psychological well-being, and patient satisfaction with medical care in the telemedicine group, compared to the face-to-face follow-up group. Finally, we aim to explore the relationship between secondary outcomes and QoL.

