### 2.5. Trial Interventions and Participant Timeline

#### 2.5.1. Stage 1

All participants will undergo a series of laboratory tests, including a complete blood count, C-reactive protein levels, and fecal calprotectin. They will also receive instrumental evaluations such as a colonoscopy with biopsy. For patients with severe IBD or jejunoileitis, a contrast-enhanced abdominal and pelvic CT scan or magnetic resonance enterography will be conducted (Table 1).

After group assignment and signing informed consent, all participants will fill out the following questionnaires:Simple Clinical Colitis Activity Index (SCCAI) [15] questionnaire for patients with ulcerative colitis/Harvey-Bradshaw index (HBI) [16] questionnaire for patients with Crohn’s disease;Short Inflammatory Bowel Disease Questionnaire (SIBDQ) [17];World Health Organization’s QoL (WHOQOL-26) [18];General Medication Adherence Scale (GMAS) [19]Patient Satisfaction Questionnaire (PSQ-18) [20];Hospital Anxiety and Depression Scale (HADS) [21];Visceral Sensitivity Index (VSI) [22];Toronto Alexithymia Scale (TAS-26) [23].

The clinical activity of the disease will be measured by Disease Activity Index (DAI) for ulcerative colitis and Crohn’s Disease Activity Index (CDAI) for Crohn’s disease [24,25].

#### 2.5.2. Stage 2

The patients in the control group will have a face-to-face consultation with a gastroenterologist, who will offer treatment recommendations, a post-discharge care plan, and dietary advice. Standard care for the control group will follow evidence-based guidelines, with outpatient visits available upon the patient’s request [24,25].

The telemonitoring group patients will receive authorized access to the personal account on the web platform. The structure of the web platform is shown on the Figure 2. It includes educational content on IBD, necessary lifestyle adjustments, and dietary guidelines, all based on international standards and resources from the Crohn’s and Colitis Foundation.

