Patients will be required to log in to the web platform at least once per month. Upon logging in, they will need to provide the following information: (1) SCCAI for ulcerative colitis and the Harvey-Bradshaw index for Crohn’s disease to assess disease activity during monitoring; (2) the IBD disk questionnaire to track disease progression; and (3) results from laboratory tests (complete blood count, C-reactive protein, and fecal calprotectin). Both healthcare professionals and patients will have access to the test results. Additionally, patients can request an online consultation with a gastroenterologist via chat or phone call. They will be advised to contact a gastroenterologist if they experience disease recurrence.

Each month, gastroenterologists will call patients in the intervention group and ask questions based on a checklist (Multimedia Appendix A). They will be trained to provide immediate assistance if there are critical deviations in health indicators from the reference values (see Table 2) or complaints suggesting the onset of an acute condition.

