### 2.7. Outcome Measurements and Data Collection Methods

The assessment of the study outcome-related variables will take place at the baseline and at 6 months post–group assignment (Table 3).

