**Figure 2 jcm-13-07734-f002:**
[figure not shown]
An online platform structure for patients in the intervention group.

**Table 1 jcm-13-07734-t001:** Summarizes the trial interventions and participant timeline.

	Study Period						
	Enrolment/Baseline 0 Weeks	Follow-Up					End of the Study (6 Months)
		1 Month	2 Months	3 Months	4 Months	5 Months	
Informed consent	X						
Eligibility criteria	X						
Demographic data	X						
Treatment in the Gastroenterology Department	X						X
Adverse events		X	X	X	X	X	X
Treatment	X	X	X	X	X	X	X
Face-to-face consultation for both groups	X						X
Observation using telemedicine technologies for the intervention group (including web-platform, phone calls)		X	X	X	X	X	
Clinical parameters							
Haemoglobin concentration	X	X	X	X	X	X	X
White blood cells concentration	X	X	X	X	X	X	X
C-reactive protein concentration	X			X			X
Fecal calprotectin concentration	X			X			X
IBD disk		X	X	X	X	X	
HBI/SCCAI questionnaire	X	X	X	X	X	X	X
Disease severity according to laboratory and instrumental data	X						X
Disease severity according to CDAI/UCDAI	X						X
Social parameters							
VSI questionnaire	X						X
TAS-26 questionnaire	X						X
HADS questionnaire	X						X
SIBDQ questionnaire	X						X
WHOQOL-26 questionnaire	X						X
Organizational parameters							
PSQ-18 questionnaire	X						X
GMAS questionnaire	X						X

**Table 2 jcm-13-07734-t002:** Limit values of the laboratory tests.

Laboratory Parameter	Critical Deviation from Reference Values
Haemoglobin concentration	Lower than 110 g/L; higher than 170 g/L
White blood cells concentration	Lower than 3 × 10^9^ cells/L; higher than 11 × 10^9^ cells/L
C-reactive protein concentration	Higher than 10 mg/L
Fecal calprotectin concentration	Higher than 200 µg/g for patients included in the trial with initially normal levels. Maintaining the level of more than 800 µg/g between two time points (Table 1) for patients included in the trial with initially high levels

**Table 3 jcm-13-07734-t003:** Study outcomes and data collection methods.

Item	Definition	Data Collection Method	Measure
Primary outcome			
Health-related quality of life (HRQol) in IBD	QoL specifically associated with bowel symptoms	SIBDQ score	Min score is 10, max score is 70. <50 means poor HRQol; >50 optimal HRQol Higher score means better outcome
Secondary outcomes			

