Generic QoL	Generic QoL associated with several domains of life quality (physical and mental health, social relationships, and environment)	WHOQOL-26 score	Min score is 0%, max score is 100% for each domain. Higher score means better outcome.
Clinical activity of UC	Clinical activity of UC according to DAI with questions regarding clinical symptoms and endoscopic activity	DAI	0–2—remission; 3–6—mild activity; 7–10—moderate activity; >10—severe activity;
Clinical activity of CD	Clinical activity of CD according to CDAI, which is a ‘gold standard’ for trials. CDAI consists of questions regarding symptoms, lab tests, extraintestinal complications, general well-being	CDAI	<150—remission; 150–300—mild activity; 301–450—moderate activity; >450—severe activity;
General medication adherence	Adherence to the prescribed medications, patient compliance	GMAS score	0–26—non-adherent; 27–33—adherent [26];
Rate of leukopenia in patients taking immunomodulators (thiopurines, cyclosporine, tacrolimus)	Leukopenia that is associated with the intake of immunomodulators according to full blood count during the monitoring	Electronic health record, full blood count	Number of patients taking immunomodulators with onset of leukopenia
Satisfaction	Patient satisfaction with healthcare	PSQ-18 score	Min score is 18, max score is 90. Higher score means better outcome;
Depression and anxiety	Levels of anxiety and depression in patients with chronic diseases	HADS	The HADS has two scales: for anxiety (HADS–A) and for depression (HADS–D), differentiating the two states. For each scale: 0–7—no depression or anxiety; 8–10—a doubtful case; 11–21—a definitive case;
Visceral sensitivity	Gastrointestinal (GI) symptom-specific anxiety causing bowel symptoms persistence	VSI score	0–10—no GI-specific anxiety; 11–30—moderate GI-specific anxiety; 31–75—severe GI-specific anxiety;
Alexithymia	Difficulty to perceive and express emotions	TAS-26 score	26–62—no alexithymia; 63–74—a doubtful case; 75–130—a definitive case;
Additional outcomes			
Endoscopic activity of UC	Endoscopic activity of UC assessed via colonoscopy	Mayo Endoscopic Score (MES)	0—normal or inactive disease; 1—mild disease with erythema, decreased vascular patterns and mild friability; 2—moderate disease with marked erythema, absence of vascular patterns, friability and erosions; 3—severe disease with spontaneous bleeding and ulceration

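### Leukopenia is counted over follow-up, but the text schedules monthly blood counts only in the telemonitoring arm, so the comparison is open to unequal detection unless Table 1 is meant to cover controls

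*Protocol article*

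**What the plan says.** The Objectives list "the rate of leukopenia in patients receiving immunomodulatory treatments (e.g., thiopurines, cyclosporine, tacrolimus") among the secondary aims. Table 3 defines the outcome as "Leukopenia that is associated with the intake of immunomodulators according to full blood count during the monitoring", takes it from the electronic health record and the full blood count, and measures it as "Number of patients taking immunomodulators with onset of leukopenia". Table 4 hypothesises lower values under telemonitoring, and Section 2.9 assigns Fisher's exact test to qualitative variables.

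The blood-count schedule is described in two places.

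- **Section 2.5.2 (Stage 2), telemonitoring arm:** "Patients will be required to log in to the web platform at least once per month", and at log-in they must supply "results from laboratory tests (complete blood count, C-reactive protein, and fecal calprotectin").
- **Section 2.5.2, control arm:** "Standard care for the control group will follow evidence-based guidelines, with outpatient visits available upon the patient’s request". Section 2.1 likewise gives controls recommendations at discharge and afterwards only when they ask. Laboratory tests for all participants appear at Stage 1 (Section 2.5.1) and Stage 3 (Section 2.5.3).
- **Table 1:** the white cell row is marked at baseline, at each of months 1 to 5 and at month 6, with no arm named.

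**The concern.** The outcome is whether leukopenia ever appeared on a count during follow-up. For such an outcome, the number of counts affects how many cases are found. If one arm is tested every month and the other once, equal true risk will tend to give unequal observed proportions, with the excess in the telemonitoring arm. Table 4 predicts the opposite. A real benefit could be hidden, or an intervention with no effect on leukopenia could appear to cause it. Randomisation does not protect against this, because the difference in testing is part of the allocated follow-up.

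**Working it through.** **1. The plan's own figure.** The only sample-size calculation is for SIBDQ (Section 2.8: SD 12.52, difference 10, power 80%, two-sided 0.05, 20% loss). n per arm = 2 × (1.960 + 0.842)² × 12.52² / 10² = 24.6, rounded up to 25; 25 / 0.80 = 31.25, rounded up to 32 per arm, or 64 in total. This reproduces the stated number. The leukopenia point does not affect it, and the document gives no figure for leukopenia.

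**2. Which schedule applies to controls?** Read literally, Table 1's white cell row covers everyone. However, the IBD disk and HBI/SCCAI rows at months 1 to 5 are equally unlabelled, and Section 2.5.2 places both on the platform that only telemonitoring patients use. Table 1 also limits the face-to-face consultation for both groups to baseline and month 6, so it gives controls no scheduled visit in between. The better-supported reading is that the unlabelled monthly rows describe the telemonitoring arm. The document does not settle it.

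**3. Size if the text governs.** All inputs here are assumptions: per-test chance p of a low count, equal in both arms; six counts under telemonitoring (months 1 to 6, every upload made); k counts in controls.

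*Independent results.* P(at least one low count in k tests) = 1 − (1 − p)^k.

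| p | Telemonitoring, 6 tests | Control, 1 test | Ratio | Control, 2 tests | Ratio |
|---|---|---|---|---|---|
| 0.01 | 5.85% | 1% | 5.85 | 1.99% | 2.9 |
| 0.03 | 16.70% | 3% | 5.57 | 5.91% | 2.8 |
| 0.05 | 26.49% | 5% | 5.30 | 9.75% | 2.7 |
| 0.10 | 46.86% | 10% | 4.69 | 19.00% | 2.5 |

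Changing p hardly moves the ratio. Adding one control test roughly halves it, and six control tests bring it to 1.

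*Persistent episodes.* Suppose onset is uniform over six months and an episode lasts L months. A single month-6 count catches a share L/6, and monthly counts catch nearly all. For L = 1, 2, 3 and 6 the shares are 17%, 33%, 50% and 100%, so the ratios are about 6, 3, 2 and 1.

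**4. Effect on the test.** This uses exact enumeration of the two-sided Fisher test at 0.05, with equal true risk, independent results and one control test. With 16 immunomodulator users per arm (assumed), the probability of a significant result showing more leukopenia under telemonitoring is 2% (p = 0.02), 23% (p = 0.05) or 51% (p = 0.10). With 8 users per arm it is 0.1%, 2.5% or 17%.

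**5. Masking.** Observed proportions are equal when 1 − (1 − p_T)^6 = p_C, that is p_T = 1 − (1 − p_C)^(1/6). For p_C = 0.05, p_T = 0.0085. In this model telemonitoring would have to cut the per-test risk by about 83% just to look the same as control.

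**The case against.** The strongest reply is that unequal testing is not established. Table 1 names an arm in some rows and none in the white cell row, so it can be read as testing both arms monthly, and then the bias disappears. Stage 2 is not a perfect guide either: it lists C-reactive protein and calprotectin among the log-in results, while Table 1 shows them during follow-up only at month 3. This stands as a reason to state the bias conditionally. It does not remove the point, because if Table 1 covers controls it contradicts a text that schedules no control test before month 6.

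The second reply is that one control test is a minimum. The health record is a named source and control care follows guidelines, so other counts may enter, and leukopenia on a continued drug may last to month 6. Both reduce the excess, which is why the range starts at about 1. Control counts made on request would still be irregular and possibly prompted by symptoms.

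A reader might also infer several stronger points that the document does not support:

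- **Conflict over timing.** Section 2.7 says "The assessment of the study outcome-related variables will take place at the baseline and at 6 months". A cumulative count compiled at month 6 fits both this and Table 3, and Section 2.1 places the leukopenia assessment at that readmission.
- **Conflicting cut-offs.** Table 2's white cell limits, "Lower than 3 × 10^9^ cells/L; higher than 11 × 10^9^ cells/L", are critical deviations that prompt assistance. Table 3's 4–11 is a normal range. Haemoglobin (110 against 120 g/L) and C-reactive protein (10 against 5 mg/L) show the same two tiers. The limits serve different purposes, and neither is named as the leukopenia definition.
- **Faulty denominator.** When immunomodulator use is fixed is detail that an article may leave to the full protocol.
- **Biased adverse-event comparison.** Monthly calls exist in one arm only, but adverse events are neither an outcome in Table 3 nor a hypothesis in Table 4.

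**Conclusion.** The point holds conditionally. Following the text of Sections 2.1 and 2.5, a follow-up-wide leukopenia count compares an arm with monthly testing against one with a single scheduled test after baseline. At equal true risk this favours finding more leukopenia under telemonitoring, opposite to Table 4. The excess could be anywhere from about 1-fold to about 6-fold. The upper end needs independent monthly results (or episodes of about one month) and exactly one control count; the lower end needs episodes that last to month 6 or frequent control testing outside the study. The document gives none of these quantities, nor the number of immunomodulator users, so a 5- to 6-fold excess should not be read as the expected size. The issue is confined to one secondary outcome in a subset of patients; the primary SIBDQ comparison and the total of 64 are unaffected. It should be corrected because, as written, a difference in either direction, or none, could not be interpreted.

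**What to change.** 1. Base the between-arm comparison on the month-6 blood count, already scheduled in both arms, among randomised patients who at baseline were on an immunomodulator and not leukopenic.
2. State one leukopenia definition for this outcome and apply it identically in both arms. The choice of threshold is the sponsor's; the limits in Tables 2 and 3 can keep their separate purposes.
3. Report telemonitoring counts from months 1 to 5 descriptively, outside the between-arm test.
4. Label the monthly rows of Table 1 by arm so that they agree with Stage 2. If controls are in fact meant to have monthly counts, say so in Section 2.5.2; unequal scheduling then no longer arises.

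The cost is a revised outcome definition and table labels, with no new tests. The real loss is that leukopenia resolving before month 6 drops out of the comparison, so the outcome becomes status at one visit rather than onset at any time during follow-up.

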### 2.1. Study Design

The TIGE-Rus is designed as a prospective, parallel, two-armed, randomized controlled trial with a 1:1 allocation.

This study will consist of three stages (Figure 1).

The first stage will be a selection of patients with IBD after treatment in the Gastroenterology Department of the Sechenov University Hospital and random assignment of participants to two groups: face-to-face outpatient observation (control group) and observation using telemedicine technologies (intervention group). For every included patient, evaluation of disease activity, QoL, medication adherence, psychological well-being, and satisfaction with medical care will be performed (Figure 1).

The second stage consists of the follow-up care. For the control group, the follow-up scheme includes face-to-face appointment and follow-up recommendations on treatment, post-discharge care plan, and diet. They will be provided with the recommendations on discharge from the hospital and then on the patient’s request. The follow-up for the intervention group consists of the following: monthly completion of questionnaires on the specialized web platform by the patient; the possibility of contacting the gastroenterologist via chat or phone call on the patient’s request; and access to educational information about IBD, psychological well-being, lifestyle, diet, sexual life, pregnancy (examples in Multimedia Appendix A), posted on the web platform. In addition, patients in the intervention group will receive a monthly phone call to address any questions or concerns they may have. During these calls, they will also be interviewed using a predefined checklist (Multimedia Appendix B).

The third stage of the study will be evaluation and comparison of follow-up efficacy in the control and intervention groups. All patients will be re-hospitalized to the Gastroenterology Department after 6 months of follow-up, where the QoL, disease activity, number of IBD relapses, frequency of leukopenia in patients receiving immunomodulators, medication adherence, psychological well-being, and satisfaction with medical care will be assessed (Figure 1).

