### 2.2. Study Setting and Eligibility Criteria

The study will be conducted in the Gastroenterology Department of the Sechenov University Hospital in Moscow, Russia. It is a national center where patients from all Russian regions are treated. Thus, the study results can be extrapolated to the entire Russian population.

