Endoscopic activity of CD	Endoscopic activity of CD assessed via colonoscopy	Simple Endoscopic Score for Crohn’s Disease (SES-CD)	0–2—remission; 3–6—mild severity; 7–15—moderate severity; >15—severe;
Histological activity of IBD	Histological activity of IBD assessed via biopsy	Binary scale	No signs of inflammation in the histological material; Presence of signs of inflammation in the histological material
Laboratory tests	White blood cells concentration; Haemoglobin concentration; C-reactive protein concentration; Fecal calprotectin concentration;	Blood test and stool test	Normal values: 4–11 × 10^9^ cells/L; 120–170 g/L; 0–5 mg/L; <200 µg/g for patients with initially normal levels. <800 µg/g in both time-points for patients included in the trial with initially high levels
General medication adherence differences	Adherence to the prescribed medications, interpreted in 5 levels of adherence	GMAS score	0–10—poor adherence; 11–16—low adherence; 17–26—partial adherence; 27–29—good adherence; 30–33—high adherence;
Rate of non-scheduled medical encounters *	Unplanned visits to the Physician for IBD symptoms	As recorded in electronic health record	Number of non-scheduled visits
Rate of surgical interventions *	Surgical interventions for IBD complications	As recorded in electronic health record	Number of surgical interventions
Rate of hospitalizations *	Unplanned hospital admissions for any reason	As recorded in electronic health record	Number of unplanned hospitalizations with specification of the reason

* we assume that telemonitoring will lead to decrease in these parameters.

**Table 4 jcm-13-07734-t004:** Hypotheses proposed according to the primary and secondary study aims.

*Hypothesis*	**H_0_**	**H_a_**	
	6 months after the start of observation, there is no difference between the groups on the evaluated parameter	6 months after the start of observation, the values of the assessed parameter are higher in the telemonitoring group	6 months after the start of observation, the values of the estimated parameter are lower in the telemonitoring group
Outcomes	All primary and secondary outcomes	HRQol Generic QoL General medication adherence Satisfaction with medical care	Clinical activity of UC/CD Rate of leukopenia in patients taking immunomodulators (thiopurines, cyclosporine, tacrolimus) Depression and anxiety Visceral sensitivity Alexithymia

H_0_—null hypothesis; Ha—alternative hypothesis.

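### The additional outcome on non-scheduled encounters counts physician visits only, so a lower count with telemonitoring could reflect a switch to chat or phone and not fewer unscheduled encounters

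*Protocol article*

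**What the plan says.** Protocol article, Table 3, additional outcomes: the row is labelled "Rate of non-scheduled medical encounters". Its definition is "Unplanned visits to the Physician for IBD symptoms", its source is the electronic health record, and its measure is "Number of non-scheduled visits". The row carries an asterisk, and the footnote reads "we assume that telemonitoring will lead to decrease in these parameters".

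The routes by which a patient can reach a physician between the two assessments are set out elsewhere:

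- **Control arm.** Section 2.5.2 describes guideline-based standard care "with outpatient visits available upon the patient’s request". Section 2.1 says of the recommendations to controls: "They will be provided with the recommendations on discharge from the hospital and then on the patient’s request".
- **Telemonitoring arm.** Section 2.5.2: "Additionally, patients can request an online consultation with a gastroenterologist via chat or phone call". The same section advises these patients to get in touch with a gastroenterologist if the disease recurs. Section 2.1 adds a monthly call at which questions can be raised.
- **Both arms.** Table 1 marks a face-to-face consultation at baseline and at 6 months only.

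**The concern.** The label promises encounters, while the definition and measure deliver visits. In many trials that would be a loose synonym. Here the intervention itself supplies a second, remote way of having an unscheduled encounter, and the count does not name it. The same event, a patient with bowel symptoms asking for a physician's help, can be recorded in one arm and go unrecorded in the other.

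The article also states in advance that it expects this outcome to fall with telemonitoring. A fall would look like confirmation, although substitution of one mode for another is enough to produce it. The risk is a reported reduction in unscheduled encounters when demand for unscheduled care is unchanged.

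**Working it through.** **Step 1: is there a planned figure to reproduce?** No. The article gives no expected rate or effect for this outcome. The sample size was set for the SIBDQ score and does not depend on this row. It does reproduce: 2 × (1.96 + 0.84)² × 12.52² / 10² ≈ 24.6, so 25 per arm; 25 / 0.80 = 31.25, so 32 per arm and 64 in total.

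**Step 2: follow one symptom-driven request in each arm, months 1 to 5.**

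| | Control | Telemonitoring |
|---|---|---|
| Scheduled face-to-face contact (Table 1) | none | none |
| On-request route described (sections 2.1, 2.5.2) | outpatient visit | chat or phone call |
| Named in the Table 3 definition or measure? | yes | no |

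A telemonitoring patient may still attend in person, and nothing in the article prevents it. The asymmetry is that only this arm has a described route outside the count.

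**Step 3: what this does to the recorded ratio.** Let both arms make unscheduled requests at the same rate r, and let a share f of telemonitoring requests be dealt with remotely. The documents do not give f, so the values below are assumptions.

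Recorded rate ratio = r(1 − f) / r = 1 − f

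- f = 25%: 0.75
- f = 50%: 0.50
- f = 75%: 0.25

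If telemonitoring also prompts in-person visits, for example after a call or an abnormal laboratory value, at a rate of g times r, the ratio becomes 1 − f + g. With f = 50% and g = 25%, it is 0.75. So neither the size nor, in principle, the net direction is fixed by the document.

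**Step 4: the same example in counts.** Assume 32 patients per arm, one request per patient over 6 months, f = 50% and g = 0. Controls have 32 visits. Telemonitoring has 32 × 0.50 = 16 visits and 16 remote contacts. The visit-only count gives 16 against 32. Counting all modes gives 32 against 32, a ratio of 1.0, which is correct because demand was set equal.

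**Step 5: would it be visible in a trial this small?** As an illustration only, Poisson counts were simulated with 32 per arm, one request per patient, equal demand, a two-sided Mann–Whitney test at 0.05 and 4,000 runs. The telemonitoring visit count was significantly lower in about 2% of runs at f = 0, 18% at f = 25%, 60% at f = 50% and 96% at f = 75%. The article does not commit to testing this row. The simulation therefore shows only that substitution on this scale need not be lost in the noise.

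**The case against.** The best defence has four parts.

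- **It is a low-tier outcome.** The row is an additional outcome. Section 2.9 plans hypothesis tests for primary and secondary outcomes, and Table 4 does not list it. This stands and limits the importance of the point.
- **Avoided in-person visits are a legitimate endpoint.** Replacing visits is part of what telemonitoring is for, and the definition says openly that visits are counted. This stands too, provided the row is named for what it counts. It does not rescue the broader label.
- **Remote contacts are not expressly excluded.** This is true: they are left out by the wording of the definition and measure, and the full protocol may say more. But Table 3 fixes definition, source and measure, and all of them describe visits.
- **The formula 1 − f only restates its assumption.** This is true. It shows the mechanism and does not estimate a bias.

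A reader might infer more than the documents support:

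- *That a decrease is guaranteed by the definition.* It is not, because monthly calls and laboratory uploads may prompt visits.
- *That every control visit is non-scheduled by definition.* The definition is limited to IBD symptoms, and controls receive a post-discharge care plan whose content is not given.
- *That records under-capture outside care, and unequally by arm.* Section 2.2 says "It is a national center where patients from all Russian regions are treated", but the article does not say what the electronic record covers. The call checklist in Appendix B asks nothing about outside visits, admissions or surgery. If the calls did reveal such care, the telemonitoring count would rise, not fall.
- *That the asterisked rows on surgery and hospitalization share the problem.* A chat cannot replace either.
- *That this figure will enter the scalability assessment.* Section 3.1 plans that assessment but does not name this outcome as an input.

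**Conclusion.** The point holds in a limited form. The label and the definition of this additional outcome do not match, and the mismatch matters because only the telemonitoring arm has a described on-request route that the definition does not name. A lower visit count could therefore come from substitution of mode alone and would not by itself show fewer unscheduled encounters or less need.

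The size is unknown. The ratios of 0.75, 0.50 and 0.25 rest on equal demand in both arms, an assumed remote share of 25%, 50% or 75%, and no visits prompted by telemonitoring. The primary outcome, the secondary outcomes and the sample size are untouched. This is an inexpensive improvement to one row of Table 3 and does not threaten the trial's main conclusions.

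**What to change.** Either of two changes to the Table 3 row would do.

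1. **Keep the label and widen the count.** Count patient-initiated contacts with a physician for IBD symptoms in both arms, by mode (visit, chat, phone), from the health record and the platform or call logs. Report the total and the in-person component. Keep the protocol's own monthly calls out of the count, since they are scheduled. Show the modes separately, because a chat message may be sent for a lesser problem than a visit and the total alone could then mislead in the other direction.
2. **Keep the count and narrow the label.** Rename the row *unplanned in-person visits for IBD symptoms*, report remote contacts beside it by arm, and state that fewer visits alone will not be interpreted as reduced need.

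The platform already has a chat module, so that part of the data arises in any case. The cost is some extra data extraction, including a log of on-request calls if none is kept. Patient care does not change.
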